### Knee examination

Evaluates the existence and degree of knee joint irregularities pertinent to knee osteoarthritis (OA) and the feasibility of safely engaging in the study. This includes assessing ligamentous instability, meniscal irregularities, flexion contractures, alignment deviations, and surgical scars.

### Recruitment strategies

To recruit participants, we implemented a multifaceted approach that included distributing informational flyers within hospital premises, posting recruitment notices on major social media platforms (e.g., WeChat and Weibo), and placing advertisements in local newspapers and community bulletin boards. We further expanded our reach by screening the patient databases of our hospital's orthopedic and rheumatology departments to identify eligible candidates. Additionally, we partnered with community organizations and established recruitment booths at health expos and senior activity centers to provide detailed information and address inquiries from potential participants.

### Enrollment and the informed consent process

Participants are enrolled in groups of 40 to ensure adequate sample sizes for each intervention arm. Baseline assessments are conducted for pre-screened participants three weeks prior to intervention commencement to secure an eligible cohort. Informed consent is obtained by the principal investigator or study coordinator before any data collection. Prospective participants are fully informed about the study, including objectives, procedures, risks, and benefits, and provide written consent.

Following informed consent, participants undergo a final eligibility verification. Those confirmed eligible are randomized into one of the three groups: Tai Chi, Baduanjin, or health education, using a computer-generated sequence. This ensures balanced group assignment and maintains the trial's integrity. A total of 120 participants will be randomized, with 40 in each group, providing sufficient statistical power to detect meaningful differences.

## Randomization and allocation concealment

To ensure the fairness and transparency of the allocation process, a computer-generated random sequence will be used to assign participants to the three intervention groups: Tai Chi, Baduanjin, and health education. The randomization sequence will be generated by an independent statistician who is not involved in participant recruitment or assessment.

Allocation concealment will be strictly maintained prior to enrollment. The randomization list will be kept in a secure, centralized system accessible only to the designated research coordinator responsible for enrollment. Until the moment of assignment, both the participants and the recruiting researchers will remain unaware of the upcoming group allocation to prevent selection bias. Participants will be randomly allocated to each intervention group with a target sample size of 40 participants per group.

Prior to randomization, all participants will undergo a detailed baseline assessment, including the pain, stiffness, and physical function subscales of the Western Ontario and McMaster Universities Osteoarthritis Index (WOMAC), as well as the Berg Balance Scale, 6-minute walk test, and SF-36 quality-of-life assessment. These baseline data will be used for subsequent statistical analyses to evaluate the effects of the interventions.

After allocation, participants will be officially enrolled into their respective study groups and begin the corresponding interventions. We acknowledge that due to the nature of these behavioral interventions, participants and instructors cannot be blinded to the group assignment after randomization. Therefore, rigorous measures have been implemented to blind outcome assessors and data analysts, as detailed in the following section. Throughout the study, we will closely monitor participants' adherence and intervention fidelity to ensure the accuracy of the results.

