### Blinding

While allocation concealment is strictly maintained until the moment of randomization, we acknowledge that blinding of participants and intervention instructors is not feasible due to the distinct nature of the interventions (physical exercise vs. health education). To mitigate the potential performance and detection biases arising from this limitation, we have implemented rigorous blinding protocols for outcome assessment and data analysis. Specifically, all research staff responsible for follow-up assessments at weeks 12, 24, and 48 will be strictly blinded to the participants' group allocation; these assessors will not be involved in intervention delivery and will be instructed neither to inquire about nor allow participants to reveal their group identity.

Furthermore, the statisticians performing the final data analysis will remain blinded to the specific group codes until the statistical analysis plan is finalized and the primary analysis is completed. To further minimize performance bias from unblinded instructors, all intervention sessions will adhere to strictly standardized manuals with neutral scripts, ensuring that encouragement remains consistent across all groups without comparative claims. Finally, the success of these blinding procedures will be evaluated at the trial's conclusion by asking assessors and participants to guess the group allocation, allowing for the calculation of a blinding index to quantify the extent of any potential unblinding.

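### The rule on who may open the randomisation list does not secure the allocation concealment that the protocol claims, and on its natural reading contradicts it

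*Protocol article*

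**What the plan says.** Three parts of the protocol article bear on this point.

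- **Randomization and allocation concealment.** On generation: "The randomization sequence will be generated by an independent statistician who is not involved in participant recruitment or assessment". On concealment: "Allocation concealment will be strictly maintained prior to enrollment". On custody: "The randomization list will be kept in a secure, centralized system accessible only to the designated research coordinator responsible for enrollment". The sentence after that gives the assurance: "Until the moment of assignment, both the participants and the recruiting researchers will remain unaware of the upcoming group allocation to prevent selection bias".
- **Enrollment and the informed consent process.** "Informed consent is obtained by the principal investigator or study coordinator before any data collection". Then: "Following informed consent, participants undergo a final eligibility verification". Only those confirmed eligible are randomised.
- **Blinding.** The assurance is repeated: "allocation concealment is strictly maintained until the moment of randomization".

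**The concern.** Concealment means that whoever decides on a participant's entry cannot know the next assignment. A secure system and independent generation do not achieve this if a person responsible for entry can open the list. Here the sole holder of access is defined by the enrolment role.

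Foreknowledge would allow consent to be pressed or not, a borderline eligibility call to go one way or the other, or the order of entry to be changed. Several features of this trial make that matter:

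- Some eligibility criteria need judgement, such as fitness for moderate exercise and severity of joint deformity.
- Baseline WOMAC, balance and walking results are known before randomisation.
- The exercise arms ask for five supervised sessions a week and the control arm for one, so there is a motive to place likely attenders in the exercise arms.
- Participants are not blinded, and the primary outcomes are WOMAC subscales.
- The primary analysis is unadjusted and imputes missing week-12 outcomes as no change, so steering on likely attendance would enter the main contrast directly.

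**Working it through.** The check is mainly a comparison of text. The article gives no figure to reproduce.

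**Step 1: who holds the list.** The custody sentence grants access to the list itself, not to a single released assignment, and grants it to one role: the research coordinator in charge of enrolment.

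**Step 2: what enrolment covers.** The section headed with that word describes consent and the final eligibility check, both before randomisation. The statement that concealment is maintained prior to enrolment also treats enrolment as the step to be protected. On this usage, the list holder is responsible for steps that must be carried out without sight of the list.

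**Step 3: is the list holder kept apart from those steps?** The independent statistician is said to be outside recruitment and assessment, but that sentence covers generation, not custody. Consent may be taken by a study coordinator. Who carries out the final eligibility check is not stated. No sentence separates the list holder from either step.

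**Step 4: compare with the assurances.** The article says that recruiting researchers do not know the upcoming allocation and that concealment holds until randomisation. The custody rule in Step 1, read with Steps 2 and 3, does not deliver this.

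**Step 5: possible size, by assumption only.** Let *k* of *n* = 40 participants in an arm be replaced by people whose expected change differs by *d* points. The arm mean shifts by (*k*/*n*) × *d*. If the other arm is steered equally in the opposite direction, the contrast shifts by 2 × (*k*/*n*) × *d*. The arm size of 40 and the planned difference of about 5.0 points come from the Sample size section. The values of *k* and *d* are assumptions.

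| *k* of 40 | *d* (points) | Shift per arm | Shift between arms | Share of 5.0 |
|---|---|---|---|---|
| 2 | 5 | 0.25 | 0.5 | 10% |
| 2 | 10 | 0.5 | 1.0 | 20% |
| 4 | 5 | 0.5 | 1.0 | 20% |
| 4 | 10 | 1.0 | 2.0 | 40% |

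If only one arm were steered, the between-arm shift would be the per-arm column, 0.25 to 1.0 points (5% to 20%).

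**The case against.** The strongest reply is that a consistent reading exists. Later in the same section, the article speaks of participants being enrolled into their arms after allocation. On that usage, the coordinator only registers people once they have been assigned, and the recruiting researchers, named separately, may be different people. The titles also differ: a research coordinator holds the list, while a study coordinator may take consent, with the principal investigator as the alternative. The article never says that the two coordinators are one person. This stands in part. It rules out the stronger inference that the person taking consent is known to see the next assignment, or that concealment is shown to be defeated. It does not rescue the rule, because the article uses the same word for the steps before randomisation and nowhere separates the roles.

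A second reply is that one-at-a-time release and the locking of records belong in a fuller protocol or a randomisation manual. That is right, and their absence here is not the point. The point is the access rule that the article does state.

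Third, baseline assessment of a pre-screened cohort, enrolment in groups of 40 and completion of baseline measures before randomisation may narrow the room for steering. They do not close it, since the final eligibility check still precedes assignment.

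Fourth, the planned secondary analyses adjust for baseline characteristics that differ between arms, including initial pain severity. This could remove part of a bias carried by measured factors. It could not remove one carried by unmeasured motivation, and it is not the primary analysis.

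Finally, the sizes are assumed. A prognostic difference of 10 points is twice the planned difference and exceeds the planned SD of 9.0, so the top of the range is an extreme case.

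**Conclusion.** The point holds as a conflict between a stated access rule and the stated assurances. As worded, the rule does not secure concealment, and on the natural reading of enrolment it contradicts the protocol's own claim.

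A reader might go further and infer that allocation will be foreseen and the trial biased. The documents do not support that: the identity of the two coordinators is left open, enrolment is used in two senses, and nothing shows that anyone would act on foreknowledge.

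The size is not derivable from the article. The range of 0.5 to 2.0 points, or 10% to 40% of the planned 5.0, rests entirely on the assumed 2 to 4 of 40 per arm, a 5 to 10 point difference and steering in opposite directions. It shows only that modest steering would not be negligible, and the conclusion does not depend on it. The point should be settled before the first randomisation, because selection on unmeasured factors cannot be undone afterwards. At submission of the article, recruitment had not begun.

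**What to change.** Change the access rule so that no one who recruits, takes consent or confirms eligibility can view the list. Let the central system, or the independent statistician, hold the sequence and release one assignment at a time, only after that participant's consent, baseline assessment and final eligibility have been recorded and locked.

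Then reconcile the sections on enrolment and consent, on randomisation and allocation concealment, and on blinding. State whether the research coordinator and the study coordinator are the same person, who makes the final eligibility decision, and in which sense enrolment is used. If practice already works this way, only the wording needs correcting.

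The cost is a change of access rights, about a paragraph of text and minor set-up work in the system. If release is not automated, some statistician time will be needed throughout recruitment. The article commits the statistician to generating the sequence but does not say that they are available to release assignments.

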### Blinding

While allocation concealment is strictly maintained until the moment of randomization, we acknowledge that blinding of participants and intervention instructors is not feasible due to the distinct nature of the interventions (physical exercise vs. health education). To mitigate the potential performance and detection biases arising from this limitation, we have implemented rigorous blinding protocols for outcome assessment and data analysis. Specifically, all research staff responsible for follow-up assessments at weeks 12, 24, and 48 will be strictly blinded to the participants' group allocation; these assessors will not be involved in intervention delivery and will be instructed neither to inquire about nor allow participants to reveal their group identity.

Furthermore, the statisticians performing the final data analysis will remain blinded to the specific group codes until the statistical analysis plan is finalized and the primary analysis is completed. To further minimize performance bias from unblinded instructors, all intervention sessions will adhere to strictly standardized manuals with neutral scripts, ensuring that encouragement remains consistent across all groups without comparative claims. Finally, the success of these blinding procedures will be evaluated at the trial's conclusion by asking assessors and participants to guess the group allocation, allowing for the calculation of a blinding index to quantify the extent of any potential unblinding.

### Study intervention

The study interventions are designed to compare the clinical effectiveness of Tai Chi, Baduanjin, and a health-education program in older adults with knee osteoarthritis. The interventions will be conducted concurrently to avoid seasonal influences on disease severity. The primary goal is to assess the impact of these interventions on pain, stiffness, physical function, and overall quality of life over a 48-week period.

During the initial 12-week period, participants in the Tai Chi and Baduanjin groups will receive supervised group training sessions, while those in the health-education group will attend weekly sessions focused on educational content related to knee osteoarthritis management. After the 12-week intervention period, participants in all groups will be followed up at Weeks 24 and 48 to evaluate the long-term effects of the interventions. There will be no additional structured intervention programs during the follow-up period; however, participants will be encouraged to continue practicing the exercises they learned during the initial 12 weeks on their own.

### Tai Chi intervention

Participants assigned to the Tai Chi group will engage in a structured training program led by experienced instructors with over five years of teaching experience. The intervention will be based on a standardized “Simplified Tai Chi” protocol, specifically adapted for individuals with knee osteoarthritis. Over the course of 12 weeks, participants will attend five 60 min sessions per week, focusing on ten selected movements designed to improve balance, flexibility, and overall physical function without excessive joint stress. These movements include the Preparatory Stance, Rolling Back, Grasping the Knee and Twisting Step, Parting the Wild Horse's Mane, Cloud Hands, Golden Rooster Stands on One Leg, Toe Kick, Embracing the Sparrow's Tail, Cross Hands, and Closing Stance (32–34). Each session will begin with a 10 min warm-up, followed by practice of the Tai Chi movements, breathing techniques, and a 10 min cool-down period with relaxation methods. In addition to the supervised sessions, participants will also attend a weekly health education lecture for 12 weeks to further support their understanding of knee osteoarthritis management.

To ensure the quality and consistency of the intervention, all Tai Chi instructors will follow a standardized teaching protocol and receive training on the specific needs of individuals with knee osteoarthritis. Participants will be encouraged to practice Tai Chi at home for at least 20 min per day, with weekly assignments provided by the instructors to reinforce learning. Adherence to the home practice will be monitored through weekly feedback forms, and the quality of the sessions will be regularly assessed through video recordings and instructor feedback. After completing the 12-week intervention, participants will be asked to continue practicing Tai Chi independently, with monthly follow-up calls from the research team to monitor adherence and provide support as needed. Follow-up assessments will be conducted at Weeks 24 and 48 to evaluate the long-term effects of the Tai Chi intervention on pain, stiffness, physical function, and quality of life.

### Baduanjin intervention

Participants in the Baduanjin group will be led by experienced instructors through a 12-week program focusing on ten specific movements of the Baduanjin exercise routine. This traditional Chinese practice, known as “Health Qigong … Baduanjin”, is standardized by the General Administration of Sport of China. The series includes the following movements: Preparatory Posture, Holding Up the Three Burns with Both Hands, Left-Right Bow and Arrow Stance, Regulating the Stomach and Spleen by Raising Hands, Seven Injuries and Laboring to Look Back, Weaving Fingers to Strengthen the Waist, Clenching Fists and Angry Gaze to Enhance Energy, and Seven Injuries and Laboring to Look Back (35–37). Each session will start with a 10 min warm-up, followed by 40 min of Baduanjin practice, and conclude with a 10 min cool-down period to ensure proper form and technique are maintained throughout the exercise.

To maintain the quality and consistency of the Baduanjin intervention, instructors will follow a standardized protocol and provide weekly assignments to reinforce home practice. Participants will practice Baduanjin daily for at least 20 min, with adherence monitored through weekly feedback. Video recordings and instructor feedback will regularly assess session quality. Both the Tai Chi and Baduanjin groups will attend weekly health education lectures. After the 12-week intervention, participants will continue practicing independently, with monthly follow-ups from the research team. Follow-up assessments at Weeks 24 and 48 will evaluate the long-term effects on pain, stiffness, physical function, and quality of life.

### Health education intervention

The Health Education intervention, designated as the control group, will focus on providing participants with essential knowledge about knee osteoarthritis and general health management. Unlike the Tai Chi and Baduanjin groups, this group will not receive any standardized exercise regimen but will instead participate in weekly health education lectures. These sessions, each lasting 60 min with a 45 min presentation followed by a 15 min discussion, will cover a range of health-related topics. To ensure content standardization, the curriculum is divided into three core modules: (1) OA Management (pathophysiology and self-care); (2) Lifestyle & Exercise Science (principles of resistance, aerobic, and flexibility training, and obesity management); and (3) Comorbidity Prevention (management of diabetes, hypertension, and seasonal dietary practices).

The goal of this intervention is to ensure that all participants, regardless of their assigned group, receive a baseline level of health education, which can help them make informed decisions about their health and lifestyle. This approach allows for a balanced comparison of the additional benefits of the standardized exercise programs in the Tai Chi and Baduanjin groups.

### Measurements

The outcome measures for our study are derived from the recommended core set by the Osteoarthritis Research Society International (27), focusing on pain, physical function, and patients' overall assessment of their knee osteoarthritis severity. Participants will be assessed at baseline (prior to the intervention), immediately after the intervention (12 weeks later), and at 24 and 48 week follow-ups (Table 1).

## Statistical analysis

All statistical analyses will be performed using SPSS Statistics version 26.0 (IBM Corp). Continuous variables will be first assessed for normality using the Shapiro–Wilk test and for homogeneity of variance using Levene's test. Data presenting a normal distribution will be expressed as mean ± standard deviation (SD). For comparisons among the three groups, one-way Analysis of Variance (ANOVA) will be used. If the ANOVA indicates a significant difference, *post-hoc* pairwise comparisons will be conducted using the Bonferroni correction to adjust for multiple testing. Non-normally distributed variables will be presented as median (interquartile range, IQR) and analyzed using the Kruskal–Wallis H test, followed by Dunn's test with Bonferroni correction for pairwise comparisons if significant. Categorical variables will be expressed as frequencies (percentages) and compared using the Chi-square test or Fisher's exact test where expected cell counts are less than 5.

For the primary outcome (change in clinical scores from baseline to post-intervention), repeated measures ANOVA will be employed, with Group as the between-subject factor and Time as the within-subject factor. If a significant interaction effect (Group × Time) is observed, simple main effects will be analyzed to determine differences between specific groups at each time point, with Bonferroni adjustments applied for multiple comparisons. A two-sided *p*-value < 0.05 will be considered statistically significant.

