### Primary outcome

The primary outcomes of our study are the changes in the Western Ontario and McMaster Universities Osteoarthritis Index (WOMAC) subscales for pain, stiffness, and physical function. These subscales are assessed at baseline and followed up at 12, 24, and 48 weeks post-intervention. The WOMAC is a widely recognized tool for evaluating knee and hip osteoarthritis, consisting of 24 items distributed across the three subscales (38). The pain subscale includes five questions scored from 0 to 10, summing up to a total of 0–50 points. The stiffness subscale comprises two questions, also scored from 0 to 10, with a total score range of 0–20. The physical function subscale contains seventeen questions, each scored from 0 to 10, resulting in a total score from 0 to 170. The total WOMAC score ranges from 0 to 240, with higher scores reflecting more severe disease. This comprehensive evaluation will allow us to assess the immediate and long-term effects of the interventions on the symptoms and functional limitations associated with knee osteoarthritis.

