### Sample size

We aim to recruit a total of 120 participants, evenly distributed across three intervention groups, with 40 participants in each group. The determination of this sample size is based on projected improvements in key outcome measures, including the Western Ontario and McMaster Universities Osteoarthritis Index (WOMAC) for pain and physical function, as well as the physical component summary of the SF-36 health survey. Our calculations are informed by the findings from relevant randomized controlled trials (RCTs) that have utilized active control conditions, which provide a robust basis for estimating the anticipated treatment effects. This sample size is anticipated to provide sufficient statistical power to detect meaningful differences in outcomes between the intervention groups while accounting for the within-study variability.

The sample size was calculated using G*Power software (version 3.1) for a one-way analysis of covariance (ANCOVA) to handle the three-group comparison, adjusting for baseline values of the primary outcome (change in WOMAC score at week 12). Key statistical parameters were determined based on findings from relevant randomized controlled trials utilizing active controls, specifically studies by Hu et al. (44) and Ye et al. (45). Effect Size (f): Given the large and robust improvements in proprioception and WOMAC function scores (*p* < 0.05) consistently reported in these studies, we anticipated a large between-group effect size of *f* = 0.32. This corresponds to an expected mean difference of approximately 5.0 points with a common standard deviation (SD) of 9.0 points. Significance Level (α): Set at 0.05 (two-tailed). Statistical Power: Set at 80% (0.80).We are conservatively factoring in a 15% dropout rate to ensure the study retains sufficient statistical power. This adjustment helps to maintain the robustness of our findings even if a portion of the participants withdraw from the study.

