### Analysis

The primary outcomes for this study are defined as the changes from baseline to Week 12 in the three WOMAC subscales: Pain, Stiffness, and Physical Function. The primary analysis will be conducted using an intention-to-treat approach, where all participants are analyzed in the group to which they were randomized, without adjustment for covariates, and with missing 12-week outcomes imputed as no change. Secondary analyses will adjust for baseline characteristics that differ significantly by treatment group, including gender, initial pain severity, medication use, disease duration, and the number of chronic conditions.

Changes in knee pain at weeks 24 and 48, along with all other outcomes, are considered secondary and will be analyzed in the same manner as the primary outcome. We will also perform a longitudinal analysis across all four time points to identify potential time trends and interactions between treatment effects and time. These analyses will utilize mixed-effects models with random intercepts for participants and fixed effects for time, considering autoregressive structures for residual errors.

To handle missing values, we will employ multiple imputation techniques under the assumption of missing at random (MAR). Given the potential for early dropout due to poor outcomes, we will also explore models that account for missing not at random (MNAR) based on informative dropout assumptions. As part of our sensitivity analyses for missing data, we will consider Bayesian models that can incorporate prior assumptions about the non-ignorable missing data mechanisms.

All statistical tests will be two-tailed, with a significance level set at *p* < 0.05. We will conduct both individual time-point analyses and longitudinal analyses to provide a comprehensive understanding of the treatment effects over time.

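### The protocol gives conflicting primary analyses (gated repeated-measures ANOVA, unadjusted week-12 change) and sizes the trial on a third (baseline-adjusted ANCOVA), without saying which governs

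*Protocol article*

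**What the plan says.** Three sections of the protocol article bear on how the primary WOMAC outcomes are tested.

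- **Statistical analysis.** The primary outcome is described as change from baseline to post-intervention, and "repeated measures ANOVA will be employed, with Group as the between-subject factor and Time as the within-subject factor". If Group × Time is significant, "simple main effects will be analyzed to determine differences between specific groups at each time point", with Bonferroni adjustment. The preceding paragraph gives a general rule for continuous variables: a Shapiro–Wilk test first, then ANOVA or Kruskal–Wallis.
- **Analysis.** "The primary outcomes for this study are defined as the changes from baseline to Week 12 in the three WOMAC subscales". The primary analysis is by intention to treat, "without adjustment for covariates, and with missing 12-week outcomes imputed as no change". A mixed model over all four time points is listed separately. Multiple imputation under missing at random is also planned, but its relation to the no-change rule is not stated.
- **Sample size.** The 120 participants come from an ANCOVA for three groups, "adjusting for baseline values of the primary outcome (change in WOMAC score at week 12"), with f = 0.32, two-sided α = 0.05, 80% power and 15% dropout.

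The Primary outcome section adds that the primary subscales are "assessed at baseline and followed up at 12, 24, and 48 weeks post-intervention".

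**The concern.** Two sections each name a different analysis for the primary outcome, and a third section powers the trial on a model that the Analysis section rules out by excluding covariates. No order of precedence is given. Whether the trial is positive could therefore depend on which section is followed, and that choice could be made after the data are seen. The stated 80% power also belongs to the ANCOVA, which neither analysis section names.

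**Working it through.** **1. The plan's own figure.** Inputs from Sample size: three groups, f = 0.32, α = 0.05, power 80%, dropout 15%. Method: noncentral F with λ = N·f², numerator df 2, denominator df N − 4 (three groups, one covariate).

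- N = 97 gives 79.9% and N = 98 gives 80.4%, so 98 are needed, or 99 for equal groups.
- With dropout, 99 / 0.85 = 116.5, so 117. The plan's 120 is consistent with this.
- With 120 randomised, 120 × 0.85 = 102 completers, λ = 102 × 0.1024 = 10.44, and power is 82%.

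The sample size reproduces as an ANCOVA. There is no arithmetic error here.

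**2. Power of the unadjusted change.** Let r be the baseline to week-12 correlation and σ the SD of a score, equal at both visits. The change has variance 2σ²(1 − r). The ANCOVA residual has variance σ²(1 − r²). If f = 0.32 is the baseline-adjusted effect, then f_change = 0.32 × √((1 + r)/2). The protocol gives no r, so a range is shown, for 102 completers:

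| r (assumed) | f_change | λ | Power | Evaluable for 80% | Randomised at 15% dropout |
|---|---|---|---|---|---|
| 0.3 | 0.258 | 6.79 | 63% | 148 | 175 |
| 0.5 | 0.277 | 7.83 | 69% | 129 | 152 |
| 0.7 | 0.295 | 8.88 | 75% | 114 | 135 |

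**3. Repeated-measures ANOVA with two visits.** With baseline and week 12 only, the interaction sum of squares is half the between-group sum of squares of the change, and the error sum of squares is half the within-group one. The halves cancel, and the df are 2 and N − 3 in both. The interaction test is then one-way ANOVA on change; a numerical check gave p-values that agreed to within 1e-14. What still differs is the handling of missing values and the gated follow-up, which compares raw scores at each visit and not changes.

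**4. Repeated-measures ANOVA with four visits.** The interaction now has (3 − 1) × (4 − 1) = 6 df and asks whether the group profiles differ anywhere over 48 weeks. Simulation assumptions: score SD 9, all visits correlated 0.5, 34 complete participants per arm, and the same effect in both exercise arms. Entries are the percentage of trials significant.

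| Effect at weeks 12 / 24 / 48 | Interaction | Week-12 change | Week-12 ANCOVA | Interaction and change disagree |
|---|---|---|---|---|
| 5 / 2.5 / 0 | 61% | 63% | 77% | 21% |
| 5 / 5 / 5 | 66% | 64% | 77% | 21% |
| 0 / 5 / 5 | 80% | 5% | 5% | 75% |

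The last row matters most. A late effect would make the trial positive under one section and give only the false-positive rate under the other.

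**5. The no-change rule.** Assume a change SD of 9, 40 randomised per arm and 15% dropout in every arm. A 5-point effect shrinks to about 5 × 0.85 = 4.25. If all arms also improve by 10 points, power in simulation falls from 62% (completers) to 50%. With no true effect, the same 10-point improvement, and dropout of 5% in control and 25% in the exercise arms, the type I error is about 16%, against 5% for completers. The missing-data rule therefore has to be settled together with the model.

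**The case against.** The best defence is that the sections can be partly reconciled. The Statistical analysis section speaks of change from baseline to post-intervention, the Analysis section fixes week 12, and the four-visit model is assigned to a separate longitudinal analysis. On that reading the repeated-measures ANOVA is the unadjusted change test (step 3). This stands as a possible reading, but the text does not settle it: group differences are to be examined at each time point, and the Primary outcome section attaches all follow-up visits to the primary subscales. Even on this reading the ANCOVA mismatch, the gate with its raw-score comparisons and the missing-data rule remain open.

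A reader might infer more than the text supports:

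- **That four rival primary tests are on offer.** Kruskal–Wallis belongs to the general rule, where "Non-normally distributed variables will be presented as median (interquartile range, IQR") and rank-tested; the primary-outcome paragraph names only repeated-measures ANOVA. ANCOVA is only the sizing basis. The protocol should say that the normality switch does not apply, but it does not name Kruskal–Wallis for the primary outcome.
- **That the gate by itself costs much power.** The omnibus figures do not show this: 61% against 63% for unadjusted change with a fading effect, 66% against 64% with a sustained one. Setting Bonferroni pairwise contrasts beside omnibus tests would exaggerate the loss.
- **That the plan discards participants with a missing visit.** Classical repeated-measures ANOVA does need complete rows, but the Analysis section plans imputation. The text conflicts; it does not commit to deletion.

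It is also fair that unadjusted change is a valid analysis and that a separate analysis plan could name one model. The first does not give it the stated power. The second does not remove a contradiction printed in the protocol itself.

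**Conclusion.** The point holds in this form and should be fixed before recruitment. The contradiction is in the text and depends on no calculation: the Statistical analysis and Analysis sections name different primary analyses, and the Sample size section relies on an adjustment that the Analysis section excludes.

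Its size depends on assumptions. On the four-visit reading, the two tests reach opposite significance decisions in about 21% of trials with an effect at week 12, and the split is 80% against 5% for an effect that appears only later. These figures rest on the assumed SD, correlation and effect pattern. The power gap (82% against 63% to 75%) rests on f = 0.32 being the baseline-adjusted effect. If f was meant for the raw change score, unadjusted change would also have 82% at 102 completers; the section names an ANCOVA but does not say which SD it used.

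**What to change.** State one primary analysis, in the same words in the Statistical analysis and Analysis sections: for each WOMAC subscale, the week-12 comparison between groups by ANCOVA adjusted for the baseline value of that subscale, in all randomised participants as allocated. This matches the Sample size section. Then:

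- Delete the repeated-measures ANOVA and the interaction gate for the primary outcome. Take the pairwise contrasts, with the Bonferroni adjustment already planned, from the ANCOVA.
- Replace the statement that the primary analysis is unadjusted.
- Say that the Shapiro–Wilk/Kruskal–Wallis switch does not apply to the primary outcome; rank tests are sensitivity analyses only.
- Make the multiple imputation under missing at random, already planned, the primary missing-data method, and keep no-change imputation as a sensitivity analysis.
- Keep the four-visit mixed model as secondary.

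The cost is a protocol wording change, with no extra participants or data. According to Study status and timeline, recruitment had not begun at submission; if it has since started, the change should be a dated amendment made before any outcome data are seen by group.
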